### Patients

All patients, 50 years of age or older, referred for an X-ray of the thoracic and/or lumbar spine, receive a short clinical questionnaire. Patients diagnosed with a VCF (Th5-L5), pain for six weeks or less and a Visual Analogue Scale (VAS) score of five and higher are contacted to participate in the study. After informed consent patients undergo a magnetic resonance imaging (MRI) scan of the spine, bone densitometry, blood sample screening and a consultation of an internist. Patients enrolled in the study comply with the following inclusion criteria: (1) VCF on X-ray of the spine (minimal 15% loss of height) [25], (2) level of VCF Th5 or lower, (3) back pain ≤ 6 weeks at time of X-ray, (4) ≥ 50 years of age, (5) bone edema on MRI of the fractured vertebral body, (6) focal tenderness on VCF level and (7) decreased bone density T-scores ≤ -1. The exclusion criteria are: (1) severe cardio-pulmonary condition, (2) untreatable coagulopathy, (3) systemic or local infection of the spine (osteomyelitis, spondylodiscitis), (4) suspected alternative underlying disease (malignancy) (5) radicular or caudal compression syndrome and (6) contra-indication for MRI. All patients contacted to participate in the study are registered in order to obtain an overview of the total patient population.

### MRI protocol

MRI is performed prior to randomization using a 1, 1.5 or 3 Tesla MRI scanner. The following MRI sequences are employed: sagittal T1 (TR 400 ms, TE 13 ms), T2 Turbo Spin Echo (TR 3500 ms, TE 120 ms) and STIR (TR 2500 ms, TE 70 ms) and transverse T2 TSE (TR 2500 ms, TE 120 ms) at the level of the affected VCF. Bone edema in the VCF is defined as increased signal intensity at the STIR images and decreased signal intensity at the T1 weighted images. The shape and grade of every VCF is scored by two radiologists using the visual semiquantitative system according to Genant (26). When there is disagreement between both observers a consensus meeting is held. The shape of the VCF is classified as wedge, biconcave or crush, depending on whether anterior, middle or posterior portion of vertebral body is most diminished in height. The grade of VCF is classified as a percentage of height reduction in mild (15-25%), moderate (25-40%) and severe (>40%).

### Interventions

The pre-procedural work-up consists of: ECG, chest X-ray and blood sampling. One hour prior to the procedure 2 g cefazolin is administered intravenously as prophylaxis. Patients are brought to the angio suite, where sterile preparation for surgery is performed. Using fluoroscopic guidance, the practitioner infiltrates the skin and subcutaneous tissues overlying the pedicle of the target vertebra or vertebrae with 1% lidocaine and infiltrates the periosteum of the pedicles with 0.25% bupivacaine (marcaine). Patients are then randomly assigned to undergo either the full PV procedure or the sham intervention. For the PV procedure, 11-gauge or 13-gauge needles are passed into the central aspect of the target vertebra or vertebrae. Bone cement is prepared on the bench and injected under constant fluoroscopy into the vertebral body. Injection is stopped when the cement reaches to the posterior aspect of the vertebral body or leaks into an extraosseous space, such as the intervertebral disk or an epidural or paravertebral vein. During the sham intervention, verbal and physical cues, such as pressure on the patient's back, are given, and the methacrylate monomer is opened to simulate the odor associated with mixing of bone cement, but the needle is not placed and cement is not injected. After the procedure, all patients are monitored in the supine position for 1 to 2 hours before discharge. Cross-over will not be offered before 6 months after randomization.

### Osteoporosis- and pain medication

All patients receive osteoporosis medication, such as bisphosphonates together with supplemental calcium and vitamin D. Pain medication demanded by the patient is recorded. Analgesics are classified following the WHO classification: (1) Paracetamol (acetaminophen), (2) Tramadol, (3) Tramadol and Paracetamol, (4) Morphine. Non Steroid Anti Inflammatory Drugs (NSAID) are only prescribed if patients are intolerant for opiate-derivatives or when already used. Corrections in dose and classification of pain medication are made if necessary.

### Clinical follow-up

An experienced nurse-practitioner requests patients to complete a standard questionnaire before and at 1 day, 1 week, and 1, 3, 6 and 12 months after the procedure. The questionnaire consist of the VAS score and questions about use of pain medication, pain location, and pain type (primary outcomes). The VAS score is a pain score ranging from 0 (no pain) to 10 (worst pain ever) [26] Questions concerning use of pain medication, pain location, and pain type are included. Secondary outcomes are back pain related disability and QOL as measured with the Roland Morris Disability (RMD) Questionnaire and the Questionnaire of the European Foundation for Osteoporosis (Qualeffo), respectively. The Qualeffo is developed specifically for patients with osteoporosis [27]. This questionnaire consists of 41 questions about: pain, physical function, social function, general health perception, and mental function. The Qualeffo score ranges from 0 (best quality of life) to 100 (worst quality of life). This questionnaire will be completed at five measurement moments (before and at 1, 3, 6, and 12 months after the procedure). The RMD questionnaire is a disability questionnaire that measures the functional status of patients with back pain [28,29]. The RMD will be completed at all measurement points. Patients visit the internist at 1, 3, 6 and 12 months follow-up. Patients receive a pain diary. Patients are asked to complete the VAS score and use of analgesics is recorded on a daily basis during the first month after randomization.

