**Methods:**

The VERTOS IV study is a prospective, multicenter RCT with pain relief as primary endpoint. Patients with a painful osteoporotic VCF with bone edema on MR imaging, local back pain for 6 weeks or less, osteopenia and aged 50 years or older, after obtaining informed consent, are included and randomized for PV or a sham intervention. In total 180 patients will be enrolled. Follow-up is at regular intervals during a 1-year period with a standard Visual Analogue Scale (VAS) score for pain and pain medication. Necessary additional therapies and complications are recorded.

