The most important differences between the two sham studies and VERTOS II is patient selection. In the sham studies both acute and chronic fractures were included while in VERTOS II only acute fractures were eligible. In addition, bone edema in the affected vertebra was not a consistent inclusion criterion in the sham studies. The sham studies lacked a control group without intervention. The discordant results from the sham studies, on the one hand, and VERTOS II, on the other hand, have incited much debate [20-24]. Apparently clinicians do still not know how to best treat their patients. The objectives of this study is to evaluate the efficacy of bone cement injection in PV for patients with acute painful osteoporotic compression fractures, as compared with a simulated placebo procedure without injection of bone cement. We hypothesize that patients who had undergone PV would report less pain at 1 day, 1 week and 1, 3, 6 and 12 months (the primary outcomes) than those in the sham control group. In addition, we hypothesize that the back pain related disability is less and the quality of life (QOL) is better of patients undergoing PV compared with patients in the simulated placebo condition

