### Sample size considerations

Conform Kallmes et al. [18], we expect a 1.5 point difference in pain relief as measured by VAS score. Given that there are seven measurement points (α = 0.05 and β = 0.20) we need 142 patients in total). Assuming a withdrawal rate of 20%, a total of 180 patients will be enrolled, 90 in each group. We used G-Power to calculate the sample size.

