### Statistical analysis

The data will be analysed according to the intention-to-treat principle. Standard statistical techniques will be used to describe characteristics of patients in both groups. We will compare baseline characteristics in the two treatment groups and if incomparability appears, we will in secondary analysis, adjust for differences. The primary outcome, significant pain relief, will be compared between groups using analysis of variance for repeated measures. If adjustment for possible baseline incomparability is needed, analysis of covariance will be done. Since we expect that the difference between the two groups will become evident from 3 months onwards, the analysis will also be performed only using scores before and 3, 6, and 12 months after the procedure.

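### The primary outcome is defined in conflicting ways and the 3-to-12-month repeat of its analysis is unranked, so trial success is not one defined event

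*Protocol article*

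**What the plan says.** The protocol article describes the primary outcome in these places:

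- Abstract, Methods: one endpoint, no time point. "The VERTOS IV study is a prospective, multicenter RCT with pain relief as primary endpoint".
- Background, final paragraph: plural, one per visit. Patients after vertebroplasty "would report less pain at 1 day, 1 week and 1, 3, 6 and 12 months (the primary outcomes").
- Clinical follow-up: plural, one per questionnaire item. "The questionnaire consist of the VAS score and questions about use of pain medication, pain location, and pain type (primary outcomes"). Disability and quality of life are then listed separately as secondary.
- Statistical analysis: singular again. "The primary outcome, significant pain relief, will be compared between groups using analysis of variance for repeated measures". No threshold for 'significant' is given, and the model term to be tested (group, or group by time) is not named.

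Sample size considerations uses one variable: "we expect a 1.5 point difference in pain relief as measured by VAS score". It continues: "Given that there are seven measurement points (α = 0.05 and β = 0.20) we need 142 patients in total".

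Statistical analysis also plans a repeat. Because a difference is expected to show from 3 months onwards, "the analysis will also be performed only using scores before and 3, 6, and 12 months after the procedure". This repeat is given no rank. The adjustment for baseline imbalance does get one: "we will in secondary analysis, adjust for differences".

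**The concern.** The four descriptions differ in the number of outcomes (one, six or four), in what is measured (a pain score, or also medication use, pain location and pain type) and in form (a score, or a relief called significant). None is said to take precedence. A later analysis plan could not settle this by adding detail, because it would have to overrule at least one published statement.

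The unranked repeat raises the same difficulty for the analysis. Its rationale, a difference from 3 months, also sits badly with the Background hypothesis of less pain from day 1. A reader cannot tell whether the early visits are part of the claim or are expected to dilute it.

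The Background justifies the trial by the conflicting results of earlier randomised trials. A trial meant to settle a dispute should leave no room to choose, after the data are seen, which variable, set of visits or model term counts as the result.

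**Working it through.** **1. The plan's own figure.** Inputs from Sample size considerations: 142 evaluable, 20% withdrawal, 180 enrolled. 142 / (1 − 0.20) = 177.5, so 178; the stated 180 agrees with slight rounding up. The 142 itself cannot be reproduced, because neither the SD nor the correlation between visits is given. For a 1.5-point difference at 80% power and two-sided 0.05, it implies an SD of 3.19 for a single comparison of means. For the between-group term of a seven-point repeated-measures analysis it implies an SD of 5.0 down to 3.5 as the correlation ρ rises from 0.3 to 0.8. What the text does fix is that 142 belongs to VAS and to seven measurement points.

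**2. Definitions side by side.**

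| Section | Number of primary outcomes | Content |
|---|---|---|
| Abstract | 1 | pain relief |
| Background | 6 | pain at each of six visits |
| Clinical follow-up | 4 | VAS, medication use, pain location, pain type |
| Statistical analysis | 1 | 'significant' relief, no threshold |
| Sample size considerations | 1 variable | VAS difference of 1.5 points |

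Only VAS appears with an effect size. No test is described for the other three questionnaire items.

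**3. Error rate if either analysis may declare success.** Assumptions: no true effect, each analysis tested at two-sided 0.05, and a range of values for ρ. The two analyses share four of seven measurements, so their results are strongly correlated. For the group effect with equal correlation ρ between visits, the correlation between the two group contrasts is

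r = √[4(1 + 6ρ) / (7(1 + 3ρ))].

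- ρ = 0.3: √(11.2 / 13.3) = 0.918; chance that at least one is significant 6.9%
- ρ = 0.5: √(16 / 17.5) = 0.956; 6.4%
- ρ = 0.7: √(20.8 / 21.7) = 0.979; 6.0%

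The percentages are 1 − P(|Z₁| < 1.96 and |Z₂| < 1.96) for a bivariate normal with correlation r. If correlation decays from visit to visit (first-order autoregressive, same three values), r is 0.802, 0.853 and 0.916, giving 7.8%, 7.4% and 6.9%.

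A simulation of both repeated-measures analyses (40,000 null trials, 71 per arm, equal correlation 0.3–0.7) gave 6.0–6.9% for the group effect and about 7.6% for group by time. If either term in either analysis could count, it gave 13–14%. Two independent tests would give 1 − 0.95² = 9.75%, which does not apply because the data overlap.

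**4. Illustration only.** Six separate visit tests at 0.05, any of which counts, would give 1 − 0.95⁶ = 26.5% if independent, and 24%, 21%, 16% and 14% at correlations of 0.3, 0.5, 0.7 and 0.8. The plan does not contain these tests.

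**The case against.** The strongest reply is that the wording is loose but the plan is not. Sample size considerations ties pain relief to VAS, and Statistical analysis plans one repeated-measures model. The label in Clinical follow-up may be a badly placed parenthesis, and a repeat introduced with 'also' reads most naturally as supportive. The article is condensed, and the division of alpha is commonly left to the full protocol or analysis plan.

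Much of this stands, and it rules out three stronger readings that a reader might infer:

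- **Each analysis is planned at 0.05.** The document gives 0.05 only as a design input, under Study design and Sample size considerations. No level is assigned to either analysis, and the absence of an alpha split is not itself a finding here.
- **A difference at any visit, or in any of four variables, counts as success.** Six visits in one repeated-measures model are not six tests, and no test is described for medication use, location or type. The 14–26% range therefore does not describe this plan.
- **A responder endpoint is intended.** No threshold or responder rate appears anywhere. The word 'significant' is imprecise, but it does not create a second endpoint.

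The contradiction itself survives. The Background and Clinical follow-up both use the plural, for different things. Clinical follow-up sets its list against a separate secondary list, so its label cannot simply be disregarded. The repeat is unranked in the same section that does label the baseline adjustment secondary. These are statements in the document, not omitted detail.

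**Conclusion.** The point holds as an internal contradiction. The primary outcome is described in incompatible ways, the 3-to-12-month analysis has no rank, its rationale conflicts with the stated hypothesis of benefit from day 1, and the deciding model term is not named.

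The effect on the type I error is conditional and modest. It is 5% if the seven-point analysis of VAS on one named term is the only primary test. It is about 6–8% if either analysis at 0.05 may succeed on one term, assuming correlations of 0.3–0.7 between visits. The document gives no correlations, so this range is an assumption. The more serious consequence is that a positive result could be disputed because what counts as positive was not fixed.

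**What to change.** Before unmasking:

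- State VAS (0–10) as the single primary variable in every section.
- State the repeated-measures analysis over all seven measurement points as the single primary analysis, and name the one model term that decides the trial. It should be the term for which 142 was calculated; the article does not show which that was. With the pre-procedure score among the seven points, the group effect averages in a pre-treatment value, so group and group by time answer different questions.
- Label medication use, pain location, pain type and individual visits secondary.
- Label the 3-to-12-month analysis supportive, or test it only after the primary analysis succeeds, and reconcile its rationale with the day-1 hypothesis.
- Replace the 'significant' relief wording by a difference in VAS score.

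Cost: a visit-specific, medication or 3-to-12-month result alone can no longer be called the primary finding. The sample size stays at 142 evaluable and 180 enrolled.

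Two alternatives cost more. Keeping both analyses as primary at 0.025 each needs about 142 × (2.241 + 0.842)² / (1.960 + 0.842)² = 172 evaluable, and 172 / 0.80 = 215 enrolled (normal approximation). Moving to a narrower contrast, such as mean VAS over 3 and 6 months, drops the 12-month visit and the seven-point basis of the calculation. If 142 came from a between-group test with equal correlations, evaluable N becomes 142 × [(1 + ρ)/2] / [(1 + 6ρ)/7], which is about 154, 186 or 231 at ρ = 0.8, 0.5 or 0.3.

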### Sample size considerations

Conform Kallmes et al. [18], we expect a 1.5 point difference in pain relief as measured by VAS score. Given that there are seven measurement points (α = 0.05 and β = 0.20) we need 142 patients in total). Assuming a withdrawal rate of 20%, a total of 180 patients will be enrolled, 90 in each group. We used G-Power to calculate the sample size.

### Statistical analysis

The data will be analysed according to the intention-to-treat principle. Standard statistical techniques will be used to describe characteristics of patients in both groups. We will compare baseline characteristics in the two treatment groups and if incomparability appears, we will in secondary analysis, adjust for differences. The primary outcome, significant pain relief, will be compared between groups using analysis of variance for repeated measures. If adjustment for possible baseline incomparability is needed, analysis of covariance will be done. Since we expect that the difference between the two groups will become evident from 3 months onwards, the analysis will also be performed only using scores before and 3, 6, and 12 months after the procedure.

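### The named primary test, repeated-measures ANOVA, uses only patients with all seven VAS scores unless values are imputed, so it fits poorly with intention to treat at 20% expected withdrawal

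*Protocol article*

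**What the plan says.** Three statements in the protocol article bear on this.

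- Statistical analysis gives the principle, "The data will be analysed according to the intention-to-treat principle", and the primary method, "The primary outcome, significant pain relief, will be compared between groups using analysis of variance for repeated measures". The adjusted version is conditional: "If adjustment for possible baseline incomparability is needed, analysis of covariance will be done". A further run is restricted to later visits: "the analysis will also be performed only using scores before and 3, 6, and 12 months after the procedure".
- Clinical follow-up sets the schedule. Patients are asked to "complete a standard questionnaire before and at 1 day, 1 week, and 1, 3, 6 and 12 months after the procedure", which is one baseline and six follow-up VAS scores, seven in all.
- Sample size considerations gives "Given that there are seven measurement points (α = 0.05 and β = 0.20) we need 142 patients in total" and then "Assuming a withdrawal rate of 20%, a total of 180 patients will be enrolled, 90 in each group".

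The article names no mixed model, likelihood-based method or imputation. It does not say what happens to a patient with a missing VAS score.

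**The concern.** Repeated-measures ANOVA, in univariate or multivariate form, works on a complete row of scores per patient. One missing score out of seven removes the whole patient, including the scores already given. A patient who withdraws at any time before 12 months is therefore lost both to the seven-score analysis and to the restricted one, since both use the 12-month score.

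Without imputation, the primary comparison would then be made among completers, while the sentence on intention to treat leads the reader to expect all randomised patients. If withdrawal depends on pain, completers in the two arms are no longer the groups that randomisation made comparable, and the estimated difference in VAS can be biased. That matters in a trial meant to resolve conflicting earlier results.

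**Working it through.** **Inputs from the article.** 142 patients needed, 20% withdrawal, 180 enrolled (90 per arm), seven scores per patient, expected difference 1.5 VAS points. The article gives no SD, no within-patient correlation and no rate of missed visits.

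**Step 1. The plan's own figure.** 142 / (1 − 0.20) = 177.5, so 178; the stated 180 agrees after rounding up. Dividing by 0.8 counts a withdrawn patient as adding no information. That is consistent with a count of completers but does not prove one is intended.

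The 142 cannot be checked uniquely without an SD and correlation. It is attainable, for instance, with the G*Power between-groups formula for repeated measures, noncentrality = N f² m / [1 + (m − 1)ρ], at m = 7, f = 0.18, ρ = 0.5: 142 × 0.0324 × 7 / 4 = 8.05, which gives 80% power. The point below does not depend on this choice.

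**Step 2. Complete cases at the planned withdrawal.** 180 × 0.80 = 144 remain and 36 are excluded. 144 is at least 142, so planned power is kept. If those 36 withdrew evenly across the six follow-up visits (assumption), each would have given (0+1+2+3+4+5)/6 = 2.5 follow-up scores on average. About 36 × 2.5 = 90 follow-up scores would be discarded.

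**Step 3. Single missed visits on top (assumed rates).** Complete cases = 144 × (1 − q)⁶, with misses independent across the six follow-up visits.

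| q per visit | Complete cases | Share of 180 |
|---|---|---|
| 0% | 144 | 80% |
| 2% | 128 | 71% |
| 3% | 120 | 67% |
| 5% | 106 | 59% |

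**Step 4. Bias, first simulation.** Assumed: SD 2.5, correlation 0.5, 20% dropout depending on the last observed VAS, scores truncated to 0–10, 400,000 patients per scenario.

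| Logit slope per VAS point | True difference | Completers' difference | Shortfall |
|---|---|---|---|
| 0.2 | 1.383 | 1.343 | 3% |
| 0.4 | 1.388 | 1.271 | 8% |
| 0.6 | 1.392 | 1.191 | 14% |

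**Step 5. Bias, second simulation.** This was a separate run with the same assumed SD and correlation, no truncation, 180 patients per trial, 1,500 trials per row, and overall dropout of about 18% to 27%. The last column is a sequential-regression estimator that uses all observed scores under missing at random. It is not a fitted mixed model but rests on the same assumption. Differences are sham minus PV.

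| Dropout mechanism | True difference | Completers | All observed scores |
|---|---|---|---|
| Unrelated to VAS | 1.5 | 1.51 | 1.51 |
| Higher VAS, both arms | 1.5 | 1.35 to 1.43 | 1.51 |
| Higher VAS, sham arm only | 1.5 | 1.18 | 1.49 |
| Opposite directions in the arms | 1.5 | 0.85 | 1.49 |
| Higher VAS, both arms | 0 | 0.00 | −0.01 |
| Higher VAS, sham arm only | 0 | −0.30 | 0.00 |
| Opposite directions in the arms | 0 | −0.53 | 0.00 |

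The completers' estimate is sound when dropout ignores pain. It is moderately too small when both arms drop out on pain in the same way, and materially off only when the mechanism differs between arms. In those last cases it can show a difference where none exists.

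**The case against.** The strongest reply is that the article does not say that patients with a missing score are dropped. Scores might be imputed first, or the term might be used loosely for a mixed model. Missing-data handling commonly sits in the full protocol or analysis plan, which is not shown, so its absence here is no fault. The article also leaves intention to treat undefined; analysing patients in their randomised arm after imputation would satisfy both sentences. All of this stands, and it makes the point conditional. It does not remove it, because the article goes beyond silence: it names a primary method which, taken at its ordinary meaning and without an added step, cannot include all randomised patients.

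Three stronger conclusions might be drawn, and the document supports none of them.

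- *The trial is underpowered.* At the planned 20% loss, 144 patients remain against 142 needed. The counts of 128 and 106 need extra missed visits at rates the article does not give.
- *The worst-pain patients will leave, mostly from the sham arm.* The article says nothing about why patients would withdraw. The larger biases in Step 5 need a mechanism that differs between arms, which is conjecture.
- *The test fails for want of sphericity.* The between-group main effect in a two-group design does not need it. Only the univariate within-patient tests do, including group-by-time, and routine corrections exist.

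**Conclusion.** The point holds in conditional form. Unless combined with imputation, the named primary test leaves out about 36 of 180 randomised patients at the withdrawal the plan itself expects, and so does not deliver the intention-to-treat analysis stated beside it. That it contradicts intention to treat outright is an inference a reader might make, but the document does not settle it.

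The exposure is bias rather than power. Where dropout follows pain in the same way in both arms, the completers' difference is roughly 3% to 14% too small. It is about 21% too small (1.18 against 1.50) or 43% too small (0.85 against 1.49) under the two arm-specific mechanisms, and unbiased if dropout is unrelated to pain. These sizes rest on assumed values and illustrate direction and order of magnitude only. Severity: should-fix.

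**What to change.** Replace the primary method with a likelihood-based linear mixed model for repeated measures on the six post-baseline VAS scores. Include every randomised patient with at least one follow-up score, in the arm assigned. Fit treatment, visit, treatment-by-visit and baseline VAS, with an unstructured covariance so that sphericity is not needed. The later-visit comparison at 3, 6 and 12 months can be read from the same model. Keep the complete-case ANOVA as a sensitivity analysis at most.

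The change costs analysis wording only: no extra patients, visits or data, and the sample size of 180 stands. There are two small downsides. Patients with no follow-up score at all still drop out of the model, and the model relies on missing at random. A sensitivity analysis for departures from that assumption should therefore be specified alongside it. If the full protocol or analysis plan already provides imputation or a mixed model, aligning the published description with it is enough.

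### The primary repeated-measures ANOVA includes the baseline score and does not say whether the group effect or the group-by-time interaction decides; neither tests the stated hypothesis of less pain after the procedure

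*Protocol article*

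**What the plan says.** - **Test.** The Statistical analysis section states that the primary outcome, pain relief, "will be compared between groups using analysis of variance for repeated measures". It names no term of that model. Analysis of covariance appears only as a conditional, secondary step if the groups turn out not to be comparable at baseline.
- **Points in the series.** The Sample size considerations section says "Given that there are seven measurement points (α = 0.05 and β = 0.20) we need 142 patients in total". Clinical follow-up has the questionnaire completed "before and at 1 day, 1 week, and 1, 3, 6 and 12 months after the procedure", which is one score before and six after. The additional analysis at 3, 6 and 12 months also keeps the pre-procedure score in the series.
- **Hypothesis.** The Background section says "We hypothesize that patients who had undergone PV would report less pain at 1 day, 1 week and 1, 3, 6 and 12 months" and calls these the primary outcomes. The hypothesis is directional and concerns post-procedure scores only.
- **Effect size.** In Sample size considerations, "we expect a 1.5 point difference in pain relief as measured by VAS score". This is not tied to a visit, an average or an interaction. "We used G-Power to calculate the sample size" does not identify the routine.
- **Expected pattern.** Statistical analysis expects the groups to separate from 3 months onwards.

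**The concern.** In a two-group, seven-point repeated-measures ANOVA, two tests bear on treatment: the group main effect (1 df) and the group-by-time interaction (6 df). They answer different questions, and neither is the question in the Background section.

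The group effect averages all seven scores. The pre-treatment score cannot respond to treatment, so it dilutes the difference and brings any chance baseline imbalance into the primary result. The interaction asks only whether the two curves differ in shape. A short-lived early benefit or a late harm could each make it significant, and it yields no difference in VAS points.

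The trial is meant to settle conflicting earlier results. A primary analysis that allows a choice between these two tests leaves room to dispute what a positive result means, and it weakens control of the 5% error rate.

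**Working it through.** **1. The plan's own figures.** 142 / (1 − 0.20) = 177.5, so 178, which agrees with the 180 in "Assuming a withdrawal rate of 20%, a total of 180 patients will be enrolled, 90 in each group". The 142 itself cannot be reproduced, because no SD or correlation is given. Solving backwards for 80% power, it fits:
- a two-sample t-test with SD 3.17;
- the seven-point group F test with SD 3.7–5.0 (correlation 0.7 down to 0.3);
- the interaction F test with f = 0.064–0.098 (same correlations).

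So the 142 does not reveal which test was powered.

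**2. Dilution of the group effect (no assumption needed).** The group effect is the mean difference over seven points:
- 1.5 points at 3, 6 and 12 months only: 1.5 × 3/7 = 0.64.
- 1.5 points at all six post-procedure visits: 1.5 × 6/7 = 1.29.

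**3. False-positive rate if either test may count.** The two tests are close to independent under no effect, so 1 − 0.95² = 9.75%. Simulation with 71 per arm gave 9.2–10.0% (10,000 runs per setting, under compound symmetry and AR(1), with a Greenhouse–Geisser correction to the interaction). Smaller sets of 3,000 runs gave 10.1–10.7%.

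**4. Power and disagreement at 142 analysed patients.** The protocol gives no SD or correlation. Assumed: SD σ = 2.5, compound symmetry with correlation ρ = 0.3, 0.5, 0.7, n = 71 per arm, two-sided 0.05. For visit differences δ_t with seven-point mean δ̄:
- Group effect: SE = √[(2/n) σ²(1 + 6ρ)/7], t with 140 df.
- Interaction: λ = (n/2) Σ(δ_t − δ̄)² / [σ²(1 − ρ)], F with 6 and 840 df.
- Disagreement (exactly one significant): g(1 − i) + i(1 − g), where g and i are the two powers.

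Example, late effect, ρ = 0.5: SE = √[(2/71) × 6.25 × 4/7] = 0.317, and 0.643/0.317 = 2.03, giving group power 52%. Σ(δ_t − δ̄)² = 3.857, so λ = 35.5 × 3.857/3.125 = 43.8, giving interaction power over 99%.

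| Pattern | Test | ρ = 0.3 | ρ = 0.5 | ρ = 0.7 |
|---|---|---|---|---|
| 1.5 from 3 months | group | 67% | 52% | 42% |
| | interaction | >99% | >99% | >99% |
| | disagree | 33% | 48% | 58% |
| 1.5 at all six visits | group | 99.8% | 98% | 94% |
| | interaction | 86% | 96% | 99.9% |
| | disagree | 14% | 6% | 6% |

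Simulation of the late pattern gave 32–56% disagreement, in line with the formula. With SD 2.5 or 3.17, correlation 0.3 or 0.5, or AR(1) at 0.7, the ranges were 32–64% (late) and 6–42% (constant 1.5).

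**5. A 1-df contrast on the six post-procedure visits.** The late pattern averages 1.5 × 3/6 = 0.75.
- Unadjusted: variance σ²(1 + 5ρ)/6; power 79%, 64%, 54%.
- Baseline VAS as covariate: variance σ²[(1 + 5ρ)/6 − ρ²]; power 87%, 87%, 94%. At ρ = 0.5, SE = √[(2/71) × 6.25 × (0.583 − 0.25)] = 0.242, and 0.75/0.242 = 3.10.

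The seven-point group effect has 67%, 52%, 42% for the same pattern.

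**The case against.** The strongest reply is that the deciding term of a named model is routine analysis-plan content, and that a condensed article may leave it there. If silence were the only issue, that would be enough. But the article fixes the model and puts the baseline score in the series. Under that model neither available test matches the hypothesis in the Background section, and an analysis plan that merely picked one would not cure this. The phrase about comparing between groups leans towards the group effect, but the expectation of a late, time-varying difference leans the other way.

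Several stronger readings do not stand:
- *The trial runs at 9.75% type I error.* Nothing in the protocol says either test suffices. The figure applies only if both readings are allowed.
- *The two tests usually disagree, or reach opposite conclusions.* Disagreement is common for the late pattern, but only about 6–14% for a constant 1.5-point effect under the main assumptions. One significant and one non-significant test are not opposite findings.
- *The interaction hardly detects a steady benefit.* With baseline in the series, a constant post-procedure effect is itself an interaction. At 1.0 point its power is 46%, 63% and 87% for correlation 0.3, 0.5 and 0.7.
- *The 80% power can simply be attached to a new contrast.* The 142 was computed for seven points with unstated inputs.

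**Conclusion.** The point holds, and the protocol should be changed. The primary test is fixed in a form that offers a diluted group effect or a directionless interaction, without choosing between them. The dilution (1.5 to 0.64 or 1.29 points) and the 9.75% under a free choice need no assumed SD. The dilution does rest on reading the seven points as including baseline, which the visit schedule and the additional analysis both support. The 9.75% rests on near-independence of the two tests and a valid sphericity correction; without the correction the interaction alone ran at about 8% under AR(1). The power and disagreement figures rest on an assumed SD and correlation and should be read as ranges.

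**What to change.** **Statistical analysis section.** Name one 1-df PV-minus-sham contrast on the post-procedure VAS scores as the sole primary test at two-sided 0.05. One example is the average over the six visits, with baseline VAS as a covariate and not one of the repeated outcomes. Report it in VAS points with a 95% CI. Treat the interaction and the visit-specific differences as supportive, unable to establish benefit alone.

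**Sample size considerations section.** State which test the 142 was computed for, with the SD, correlation and G-Power routine used. Then recompute power for the named contrast instead of reassigning the 80%.

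**Cost.** New wording plus a real power recalculation, made before unblinding, with no new data collection. Whether 142 evaluable patients give 80% power for the new contrast is known only after that recalculation. A significant interaction alone could no longer be claimed as success. An equal-weight average is also less sensitive than the interaction to an effect confined to some visits: for the late pattern, about 87–94% with baseline adjustment against over 99%.
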